#### Anthropometric measurements

Waist and hip circumferences were measured using SECA Bodymeter 206 (SECA GmbH & Co. KG, Hamburg, Germany). For waist circumference measurement, the measuring tape was positioned two finger widths above the umbilicus. Hip circumference measurement was recorded at the midpoint or widest region of the buttock.

#### Body composition analysis

Height (cm) and weight (kg) were measured using InBody Stadiometer BSM370 (InBody Co., Ltd., Seoul, South Korea). Body composition, including fat and lean mass, was evaluated via a bioelectrical impedance analysis using the InBody 770 analyzer (InBody Co., Ltd., Seoul, South Korea). Participants were instructed to stand barefoot on the device platform and follow the on-screen prompts to ensure standardised measurements conditions [54].

#### Cardiovascular assessment

Blood pressure and arterial stiffness were measured after 15 min of supine rest using SphygmoCor-XCEL device (AtCor Medical Pty Ltd., Sydney, Australia). Brachial systolic and diastolic pressures were measured using an automated cuff. Carotid-femoral pulse wave velocity (cf-PWV) was measured by applying a tonometry probe to the carotid artery and inflating a thigh cuff. Each measurement was performed up to 10 attempts to capture regular pulses.

#### Handgrip strength test

Handgrip strength was assessed using a Jamar Plus + dynamometer (Sammons Preston Rolyon, USA). Participants were requested to stand upright with the elbow flexed at 90° and the forearm in a neutral position. Maximum grip force was recorded in three attempts per hand, with a 60-s rest interval between alternate attempts [55].

#### Skin advanced glycation end product assessment

Skin accumulation of advanced glycation end products (AGEs) was assessed non-invasively using AGE Reader device (DiagnOptics Technologies B.V., Groningen, Netherlands). Measurements were performed on the dominant forearm that was cleaned with an alcohol wipe before placing it on the device. Three consecutive readings were taken per participant [56].

#### Lifestyle monitoring

Biometrics data [57] were collected with an OURA ring (Oura Health Ltd., Oulu, Finland), which was provided to participants at baseline and worn throughout the study. This device passively monitors physical activity (daily steps and activity intensity) and sleep duration throughout the intervention period. Data were synchronized via the OURA app and used to monitor adherence to sleep and physical activity recommendations, as well as to track behavioural changes over time.

#### Questionnaires

Sociodemographic characteristics were obtained using self-reported questionnaires. Wellness status was assessed using a wellness questionnaire. Mental wellbeing including depression, anxiety, and/or stress levels was assessed with Depression Anxiety and Stress Scale (DASS-21) [58]. Food intake was assessed using a 3-day food diary completed by participants after the baseline and end-of-intervention visits. Participants recorded all foods and beverages consumed on two weekdays and one weekend day [59]. Quality of life was assessed with the 36-Item Short Form Survey (SF-36) [60] and EuroQol-D5-5L (EQ-5D) [61]. Reproductive health was assessed by Androgen Deficiency in Aging Males (ADAM) [62] and Brief Sexual Function Inventory (BSFI) [63] questionnaire for males and Female Sexual Function Index (FSFI) [64] questionnaire for females. Oral health status and mucosal screening was conducted using the Geriatric Oral Health Assessment Index (GOHAI) [65] and the Self-reported Oral Health Questionnaire developed by Centers for Disease Control and Prevention (CDC) and the American Academy of Periodontology (AAP).

#### Qualitative assessment

Semi-structured qualitative interviews were used to explore both participants’ experiences, motivation, and views of trial participation and their engagement with (and evaluation of) precision geromedicine programmes more generally. These data assist in identifying how the trial design and the clinical translation of interventions can be personalised to participants’ experiences, values, and concerns, supporting ethical practice and conduct of research. Interviews lasting between 30 and 60 min were conducted at two time-points: at the point of recruitment and at the completion of the study. Reflexive thematic analysis on transcripts was undertaken to identify key themes in ways that ensure interpretive depth, transparency about analytical decisions, and researcher reflexivity [66, 67]. The interview topic guide was shaped by insights into motivation and awareness from interview studies conducted locally [68, 69] but extends these to also explore personal values and concerns.

#### Safety assessments

Information regarding the occurrence of adverse events (AEs), either reported by the participants or inquired by researchers, were systematically captured in digital database throughout the study. Given the concurrent administration of multiple supplements, safety monitoring was implemented throughout the study. All selected supplements have established safety profiles at the doses used (Table 3). Participants with any medical conditions deemed by the principal investigator (PI) as potential contraindications were excluded at screening based on medical history review. Any adverse events were recorded with temporal relation to the intervention period. Should clinically significant intolerability occur, dose adjustment, temporary discontinuation, or permanent cessation of the respective supplement was at the PI’s discretion. All collected AEs were recorded according to the Medical Dictionary for Regulatory Activities (MedDRA) and graded according to CTCAE (version 6.0) [70]. Duration (start and stop dates and times), seriousness, severity/grade, outcome, concomitant medication use, action taken, and relation to study intervention were recorded. An AE was considered a serious adverse event (SAE) if it fulfilled the International Council for Harmonization (ICH) Good Clinical Practice (GCP) guideline criteria based on the PI’s clinical judgement. Each SAE is required to be reported within 24 h of learning of its occurrence. The PI is required to complete the SAE Report Form, assess the causal relationship to study intervention, and send the completed form to the National University of Singapore Institutional Review Board and to Singapore’s Health Sciences Authority [71].

#### Sample size

This study was designed to assess the preliminary effectiveness and feasibility of a precision geromedicine multimodal intervention. For the semi-finals stage, the XPRIZE guidelines focused on developing a small pilot study including around 5 to 20 participants. We opted for the larger sample size and, therefore, 20 participants were included. This sample size reflected the feasibility considerations and provided preliminary data on recruitment rates and outcome variability within the target population [20].

### Statistical and analytical plans

Adherence to each intervention component (sleep, dietary recommendation, supplementation, and exercise) will be analysed descriptively. Adherence will be summarised across the intervention period using mean and standard deviation (SD) or median and interquartile range (IQR) where appropriate. Adherence will be additionally categorised using a predefined threshold of ≥ 80% to indicate adequate adherence. The proportion of participants meeting this threshold will be reported for each intervention component.

Changes in outcome measurements at the mid-intervention and the end-of-intervention compared to baseline will be calculated for each participant. Continuous outcomes will be summarised as mean changes with 95% confidence intervals (CIs) for approximately normally distributed data or as median changes with interquartile ranges (IQRs) for non-normally distributed data. Within-participant changes from baseline to each follow-up timepoint will be assessed using paired t-tests or Wilcoxon signed-rank tests, as appropriate.

To evaluate longitudinal changes across all study timepoints while accounting for within-participant correlation, linear mixed-effects models will be applied for continuous outcomes. Timepoint will be included as a fixed effect, and participant ID will be included as a random effect. Estimated marginal means and corresponding 95% CIs will be reported for each timepoint, together with model-based contrasts comparing mid- and end-of-intervention with baseline.

To account for multiple testing across outcome measures, the Benjamini–Hochberg procedure will be applied to control the false discovery rate. All statistical tests will be two-sided, given the small sample size (*n* = 20), *p* values will be interpreted descriptively and hypothesis-generating only, and 95% CIs will be reported where applicable to support estimation of effect magnitude and precision.

Data will be visualized in spaghetti plot to display the changes during the intervention trajectory at individual level and the group level. All data analysis and visualization will be performed using R.

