Lifestyle, including diet and physical activity, can modulate fundamental biological processes of ageing [4, 6]. Regular physical activity, adherence to a healthy diet, optimised sleep, and mitigation of lifestyle risk factors (e.g. smoking) are associated with a higher lifespan and healthspan by approximately 4–10 years [7]. Nutraceuticals, encompassing a broad range of compounds, have also shown potential geroprotective effects in clinical trials in humans [8, 9]. Nutraceuticals such as whey protein and creatine can enhance muscle protein synthesis, preserve lean mass, and improve strength, with additive benefits when combined with exercise [10]. Other compounds, including fucoidan and nicotinamide mononucleotide (NMN), have been associated with immune and mitochondrial health [11, 12], ergothioneine with antioxidant and neurovascular protection [13], urolithin A with improved mitochondrial function and muscle endurance [14], and multivitamins with cognitive and metabolic health, particularly in at-risk or nutritionally deficient populations [15].

A shift from conventional unimodal therapies toward multimodal interventions is emerging, as combined strategies may exert additive effects across multiple biological mechanisms of ageing and thereby promote healthspan. Multimodal trials such as the Finnish Geriatric Intervention Study to Prevent Cognitive Impairment and Disability (FINGER) study demonstrated that combining dietary intervention, physical exercise, cognitive training, and vascular risk monitoring preserved cognitive function in at-risk older adults from the general population [16]. In addition to these findings, a population-based cohort study demonstrated that modest combined improvements in sleep, physical activity, and diet quality can achieve meaningful lifespan and healthspan benefits, suggesting that multimodal approaches compared to single domain interventions may be more effective by producing additive effects [17]. However, trials, including the Multidomain Alzheimer Preventive Trial and the DO-Health study, did not find significant improvements in clinical outcomes with their multimodal approach [18, 19]. These inconsistent findings likely reflect substantial inter-individual variability, underscoring the necessity of gerotypes with aligned corresponding gerointerventions.

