#### Screening and enrolment

Participants who met the eligibility criteria and did not fulfil any exclusion criteria during pre-screening were invited to attend an in-person screening visit. At the screening visit, participants received detailed information about the study’s purpose, procedures, risks, and requirements and provided written informed consent. Recruitment commenced in July 2025 and finished in December 2025. The final participant completed the last study visit on 23 February 2026. The study is currently in the biomarker measurement and analyses phase.

Participants were assessed at baseline, during which they underwent evaluations of muscle mass and function, cognitive function, immune function, biological markers, anthropometric measurements, and clinical and digital measurements. Follow-up assessments were conducted at the mid-intervention (week 4) and at the end-of-intervention (week 8), as shown in Table 2.

**Table 2 Tab2:** Overview of assessments performed at each study visit

Measurement	Pre-screening	Screening	Baseline	Week 4	Week 8
**Informed consent**	•	•			
**Lifestyle and medical questionnaire**	•				

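### As described, the mixed model gives the week-4 and week-8 changes one shared standard error, so its 95% confidence intervals can be miscalibrated in either direction and can disagree with the planned paired intervals

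*Protocol article*

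**What the plan says.** The Statistical and analytical plans section of the Protocol article analyses change in continuous outcomes in two ways.

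- **Paired analysis.** "Within-participant changes from baseline to each follow-up timepoint will be assessed using paired t-tests or Wilcoxon signed-rank tests, as appropriate". Approximately normal outcomes are summarised as a mean change with 95% CI, the others as a median change with IQR.
- **Mixed model.** "Timepoint will be included as a fixed effect, and participant ID will be included as a random effect". It yields estimated marginal means and "model-based contrasts comparing mid- and end-of-intervention with baseline". No random slope, residual covariance or unequal variance is mentioned.

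Both address the same two changes, and the section does not say which governs. It treats p values as descriptive and puts the weight on intervals: "95% CIs will be reported where applicable to support estimation of effect magnitude and precision".

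Two design features bear on the choice. The Introduction says of earlier multimodal trials that "These inconsistent findings likely reflect substantial inter-individual variability", and uses this to justify tailoring. The Augmented intervention section then has supplementation continued or changed at week 4 according to each participant's own progress.

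**The concern.** With three visits, a random intercept makes the variance of the difference between any two visits the same. One pooled standard error then serves both contrasts with baseline. If the three differences are not equally variable, that standard error is too small for some contrasts and too large for others.

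Equal variability is a strong assumption here. The rationale for the trial is that people respond differently, and the week-4 adjustment intervenes on that response halfway through.

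The stake is the stated purpose of the intervals. They are meant to convey magnitude and precision and, according to the abstract, the findings will inform a 12-month randomised trial. The same change could also appear with two intervals of different width and no rule for choosing between them.

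**Working it through.** **Inputs from the article.** n = 20, single arm (Sample size); three visits, at baseline, week 4 and week 8 (Screening and enrolment); two-sided tests and 95% CIs (Statistical and analytical plans). The article states no SD, effect size or power, so there is no figure of its own to reproduce.

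**Assumed quantities.** s is the residual SD; t4 and t8 are the SDs of true individual change at weeks 4 and 8; r is the correlation of those changes. The larger of t4 and t8 is varied from 0.5s to 3s.

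**Variances of the three differences**

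- V(0–4) = 2s² + t4²
- V(0–8) = 2s² + t8²
- V(4–8) = 2s² + t4² + t8² − 2·r·t4·t8

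**Standard errors, complete data**

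- Random intercept, either contrast: SE² = [V(0–4) + V(0–8) + V(4–8)] / (3n)
- Paired analysis: SE² = V(own difference) / n
- Week-8 ratio, model to true: √{[V(0–4) + V(0–8) + V(4–8)] / [3·V(0–8)]}

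The week-8 interval is too narrow only if V(0–4) + V(4–8) < 2·V(0–8), which reduces to 2·t4² − 2·r·t4·t8 < t8².

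**Check of the identity.** In one simulated dataset the fitted random-intercept model gave 0.4103 for both contrasts, as did the formula. The paired standard errors were 0.486 (week 8) and 0.276 (week 4). Adding a random slope in time raised the week-8 value to 0.486.

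**Results.** The variances and SE ratios below take s = 1 and the larger response SD equal to 2. For linear divergence, t4 = 1, t8 = 2 and r = 1, so the variances are 3, 6 and 3, and the week-8 ratio is √(12/18) = 0.82. Coverage comes from 40,000 simulated trials per setting, n = 20, no dropout, with (20 − 1)(3 − 1) = 38 df for the model and 19 for the paired interval. It is shown as the larger response SD goes from 0.5s to 3s.

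| Pattern of response | V(0–4), V(0–8), V(4–8) | SE ratio wk 4 | SE ratio wk 8 | Coverage wk 4 | Coverage wk 8 |
|---|---|---|---|---|---|
| Linear divergence (t4 = t8/2, r = 1) | 3, 6, 3 | √(12/9) = 1.15 | √(12/18) = 0.82 | 95.3% → 98.1% | 94.2% → 87.0% |
| Complete by week 4, persists (t4 = t8, r = 1) | 6, 6, 2 | √(14/18) = 0.88 | 0.88 | 94.6% → 90.3% | 94.5% → 90.3% |
| Equal spread, r = 0.5 | 6, 6, 6 | 1.00 | 1.00 | about 95% | about 95% |
| Equal spread, r = 0 | 6, 6, 10 | √(22/18) = 1.11 | 1.11 | 95.5% → 97.1% | 95.2% → 97.0% |
| Catch-up after week 4 (t8 = t4/2, r = 1) | 6, 3, 3 | √(12/18) = 0.82 | √(12/9) = 1.15 | 94.4% → 86.6% | 95.4% → 98.1% |

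Under linear divergence, week-8 coverage is 92.8% when t8 = s and 89.1% when t8 = 2s. Over the full range the model interval is 0.95 to 0.75 times as wide as the paired one. With no variation in response, model coverage is 95%. The paired interval holds about 95% in every setting.

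**The case against.** **An unseen analysis plan may say more.** The article says only that participant is a random effect, and covariance details are often left to the SAP. That is fair as to omissions. But the article does state a structure, and a plan that followed the sentence in its ordinary sense would inherit the restriction.

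**Variable response does not imply a week-8 interval that is too narrow.** A reader might infer this from the talk of heterogeneity. The documents do not support it. They give no SDs and no pattern over time, the remark on variability concerns earlier trials, and changing treatment for those who miss their threshold could let them catch up, which reverses the direction. This objection stands in full.

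**The model does not assume that everyone responds equally.** Correct. Differences in response go into the residual, so part of that variation is still counted.

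**A valid interval is already planned.** Also correct: the mean paired change with 95% CI is calibrated for approximately normal outcomes. It would be wrong to say that all the trial's intervals are at fault. What remains is that the model intervals will stand beside the paired ones with no stated order of precedence.

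**Two further inferences go beyond the text.** The Benjamini–Hochberg procedure is applied across outcome measures; the article does not say that both p values for a contrast enter it. Nor does it say that CD4/CD8 is modelled untransformed; it is silent on transformation.

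**The trial is exploratory.** This softens the p values, but not the intervals on which the plan relies for precision.

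**Conclusion.** The point holds in a limited form. On its natural reading, the stated model ties the week-4 and week-8 contrasts to one standard error, and nothing in the design makes the required equality of variances likely. The direction of any error cannot be known in advance. Over the assumed range of variance ratios it goes from none to a loss of about 8 percentage points of coverage in one contrast, with over-coverage of up to about 3 points in the other under divergence or catch-up. At the low end (response SD half the residual SD) the effect is under one point.

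These figures assume normal data, no dropout and the five patterns shown; the variance ratios are illustrations, not estimates from the trial. Whatever the pattern, two smaller matters remain: the article names no governing analysis for a change that it analyses twice, and for non-normal outcomes it plans a median with IQR, which describes spread between participants and not the precision of the estimate.

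**What to change.** 1. Replace the random-intercept sentence with a repeated-measures model: visit as a fixed effect, unstructured 3×3 covariance across the visits, REML, Kenward-Roger degrees of freedom. This needs no assumption about how response spreads over time. A random slope on linear time would be a partial remedy, but it still imposes a pattern.
2. Name this model as the governing analysis of each contrast with baseline and keep the paired test as a check. State that each contrast contributes one p value to the Benjamini–Hochberg procedure.
3. For outcomes analysed by Wilcoxon test, add a Hodges-Lehmann estimate with 95% CI to the median and IQR.

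**Cost.** A few lines of plan text and R code. The covariance has six parameters instead of two, estimable from 20 participants at three visits. Some intervals may widen. Even where compound symmetry is true, the paired interval, which the unstructured model essentially reproduces with complete data, is about 3% wider than the random-intercept one (simulated width ratio 0.97). The article says that measurement and analysis are under way, so the change should be dated and recorded as made before or after the outcome results were seen.

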#### Augmented intervention

This intervention was given based on participant’s assessment outcomes. At baseline, participants with (1) lower levels of muscle mass (below the 50th percentile for age and sex normative data as provided by InBody 770 analyzer (InBody Co., Ltd., Seoul, South Korea) received urolithin A (500 mg/day, Urolithin A Veggie Capsules: StanYouth® Urolithin A, Bonerge, China), (2) lower levels of VO_2_peak (below the 50th percentile for age and sex normative data) [21] received NMN (300 mg/day, AbinoNutra® NMN, Abinopharm, Inc., USA), and (3) cognitive performance below the 50th percentile for their age- and sex-group based on the NIH Toolbox Cognition Fluid Composite score [22] received a sex-specific multivitamin-multimineral supplement (1 tablet of 1.2 g/day, Centrum, USA). At the mid-intervention time point, the primary outcomes were evaluated to determine the individual progress and potentially adjust the intervention protocol. Based on the decision tree presented in Fig. 2, the intervention initiated at baseline was continued (if the improvement threshold or expected direction of changes is achieved) or adjusted (if the improvement threshold or expected direction of changes is not achieved). The augmented intervention was adjusted by (1) increasing the dose of a given supplement and/or (2) including another supplement. Specifically, if the threshold of improvements in muscle mass and VO_2_peak is not attained, the dose of urolithin A and NMN increased to 1000 mg and 600 mg, respectively [14, 28, 29]. If the threshold of changes in cognition was not achieved, ergothioneine (L-Ergothioneine Veggie Capsules: Dr.Ergo® L-ergothioneine, Shanghai EGT Synbio Group, China and Abinopharm, Inc., USA) was administrated (25 mg, 3 times per week) [30]. Lastly, if the expected direction of changes in immune function is not achieved, the dose of fucoidan was increased to 3.6 g/day [27]. The supplementation strategies and rationale are presented in Table 3.

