NMN	300 mg/day given if VO_2_peak (mL/kg/min) is below the 50th percentile for age and sex normative data	600 mg/day given if VO_2_peak (mL/kg/min) improvement is below 0.6 for men or 0.7 for women	Normative values in Chinese adults [21]. The cut-off threshold for dose escalation comes from scaled values based on the 10–20 years younger target in the planned 1-year intervention	NMN is safe up to 900 mg/day for 60 days [28]. NMN is a precursor of NAD⁺, a key cofactor in cellular metabolism [11]. Increasing NAD⁺ levels enhances mitochondrial function, energy metabolism, and physical performance, including improvements in aerobic capacity (as measured by VO₂peak) [44]
Multivitamin-multimineral	1 tablet given if cognitive performance score is below the 50th percentile for age and sex normative data based on the NIH Toolbox Cognition Fluid Composite score [45]	Continue dose as baseline	NIH Toolbox Cognition Battery database	Multivitamin-multimineral supplementation is widely used globally and helps correct subclinical micronutrient deficiencies that may impair cognitive function and immune health [45]. Adequate micronutrient status is essential for neuronal function, neurotransmitter synthesis, and immune regulation [15]
Ergothioneine	Not prescribed	25 mg (3 times per week) given if cognitive performance score improvement is below 1.3 for men or 1.0 for women [30]	NIH Toolbox Cognition Battery database	Three times 25 mg per week ergothioneine supplement was safe and induced significant improvement in previous clinical trial [30], and its combination with exercise also showed additive benefit on cognition [13]

*ATP*, adenosine triphosphate; *NAD*, nicotinamide adenine dinucleotide; *NIH*, National Institutes of Health; *NMN*, nicotinamide mononucleotide; *VO*_*2*_*pe**ak*, peak oxygen uptake

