#### Biological sample collection and analysis

From overnight fasting peripheral blood drawn at each study visit, five fractions were collected: whole blood, serum, plasma, peripheral blood mononuclear cells (PBMCs), and buffy coat. Blood samples collected in K2-EDTA tubes and serum separator tubes (SST™) (BD Vacutainer®, Becton Dickinson) were centrifuged at 1200 × g for 15 min with soft brake to obtain plasma and serum, respectively. Prior to centrifugation, whole blood was aliquoted from the K2-EDTA tube and will be used for the measurement of nicotinamide adenine dinucleotide (NAD) concentrations using the Q-NADMED Blood NAD + and NADH Assay Kit (NADMED Ltd., Helsinki, Finland), according to the manufacturer’s instructions. Plasma will be used for proteomics profiling using SomaScan® 11 K Assay (SomaLogic Operating Co., Boulder, CO, USA). Untargeted metabolomics in plasma will be performed using a Vanquish UHPLC system coupled to an Orbitrap Exploris™ 120 high-resolution mass spectrometer (Thermo Fisher Scientific, Germany), with chromatographic separation on a Hypersil Gold column (100 × 2.1 mm, 1.9 μm; Thermo Fisher Scientific, USA) and an ACQUITY UPLC BEH Amide column (Waters, Ireland). Serum was collected for quantification of cytokines interleukin-6 (IL-6), IL-10, tumour necrosis factor-alpha (TNF-α), and IL-1β using the Cytokine 4-Plex A assay (Quanterix, Billerica, MA, USA) according to the manufacturer’s instructions, with detection performed by multiplex immunoassays on the Luminex® xMAP® platform (Luminex Corporation, Austin, TX, USA). Biochemical blood tests, comprising haematology, liver and renal function profiles, lipid profile, glucose, glycated haemoglobin (HbA1c), insulin, and high-sensitivity C-reactive protein (hs-CRP), were conducted by an accredited clinical laboratory. The neutrophil-to-lymphocyte ratio (NLR) was derived from biomedical blood tests to assess systemic inflammatory status. The PBMCs were isolated from whole blood collected in acid citrate dextrose solution A (ACD-A) tubes (BD Vacutainer®, Becton Dickinson) through density-gradient centrifugation using Ficoll-Paque™ PLUS (Cytiva, Marlborough, MA, USA), cryopreserved in foetal bovine serum (FBS) (Gibco, Thermo Fisher Scientific, Waltham, MA, USA) containing 10% dimethyl sulfoxide (DMSO) (Sigma-Aldrich, Merck KGaA, Darmstadt, Germany), and stored in liquid nitrogen for downstream immune-function assays.

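### Whole-blood NAD is planned only as a whole-group change over time, although by design only some participants start NMN, so the result will not show whether NMN reached its stated target

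*Protocol article*

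**What the plan says.** Under Statistical and analytical plans, the Protocol article summarises each continuous outcome by its change from baseline over all participants, with paired tests. In addition, "linear mixed-effects models will be applied for continuous outcomes". The model's content is fixed in one sentence: "Timepoint will be included as a fixed effect, and participant ID will be included as a random effect". Supplement received does not appear as a model term, a subset or a summary. Spaghetti plots will show individual and group trajectories, with no stated split by supplement.

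Under Biological sample collection and analysis, a secondary-outcome section, whole blood from each study visit "will be used for the measurement of nicotinamide adenine dinucleotide (NAD) concentrations".

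Under Augmented intervention, participants with VO2peak below the 50th age- and sex-specific percentile "received NMN (300 mg/day"). Table 3 gives the same rule: "300 mg/day given if VO_2_peak (mL/kg/min) is below the 50th percentile for age and sex normative data". Its rationale column describes NMN as a NAD+ precursor and attributes the expected benefit to higher NAD+. Table 1 admits participants up to the 75th VO2peak percentile, so those between the 50th and 75th can enrol without starting NMN. At week 4 the NMN dose depends on the VO2peak response.

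**The concern.** The protocol names a biochemical target for one of its personalised supplements and measures that target. The stated analysis then averages NAD over people who were and were not given the supplement. The resulting number describes the group as a whole and does not relate NAD to NMN.

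This matters because the Discussion presents the study as a test of individualised, mechanism-informed programmes. The Statistical section also says that confidence intervals are there to support estimation of effect size and precision. A small pooled NAD change could mean that NMN did little, or that it worked in a minority. A large one could come from NMN or from the exercise, diet and other supplements that everyone received. A split by NMN receipt would help to separate these readings, and the planned summary does not provide it.

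**Working it through.** **Inputs from the Protocol article.** There is a single arm of 20 ("We opted for the larger sample size and, therefore, 20 participants were included"), chosen within the competition's range of 5 to 20. No power, effect size or SD is stated, so there is no planned figure to reproduce. "All statistical tests will be two-sided"; alpha of 0.05 is assumed from the 95% intervals.

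**Inputs that are assumptions.** The share f starting NMN is not reported. If VO2peak percentiles were uniform below the 75th, f = 50/75 = 0.67, about 13 of 20 (binomial 95% range 9 to 17); 5 to 20 recipients are shown below. The recipients' NAD change is d standard deviations of individual change, with d from 0.5 to 1.5. Non-recipients change by 0. Within-group SD is 1.

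**Step 1: what the time-only model estimates.** With complete data, the time contrast of a random-intercept model equals the mean change over all participants. A fit to simulated data for 20 people and three visits confirmed this: contrasts of 0.804 and 0.687, identical to the mean changes. Hence

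pooled change = f × (recipients' change) + (1 − f) × (non-recipients' change).

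With no change in non-recipients this is f × d. At 13 of 20, f = 0.65, so the pooled change is 65% of the recipients' change.

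**Step 2: spread.** Mixing the two groups gives a pooled SD of √(1 + f(1 − f)d²). At f = 0.65 and d = 1.0 this is √(1 + 0.2275) = 1.108, so the standardised pooled change is 0.65/1.108 = 0.587.

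**Step 3: information.** The noncentrality of the pooled paired test (n = 20) relative to recipients only (n = 20f) is √f / √(1 + f(1 − f)d²), which is below 1 whenever f < 1. At f = 0.65 and d = 1.0 it is 0.806/1.108 = 0.73. Power for d = 1.0, two-sided:

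| Recipients of 20 | Pooled change | Pooled SD | Power, pooled | Power, recipients only | Power, recipients v non-recipients (normal approx.) |
|---|---|---|---|---|---|
| 5 | 0.25 | 1.090 | 16% | 40% | 49% |
| 10 | 0.50 | 1.118 | 48% | 80% | 61% |
| 13 | 0.65 | 1.108 | 70% | 91% | 57% |
| 16 | 0.80 | 1.077 | 88% | 96% | 43% |
| 20 | 1.00 | 1.000 | 99% | 99% | – |

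At 13 recipients, pooled versus recipients-only power is 27% v 38% for d = 0.5, 54% v 75% for d = 0.8, and 92% v more than 99% for d = 1.5.

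**Step 4: precision of the added contrast.** The 95% half-width of the difference in change is t(0.975, 18) × √(1/n₁ + 1/n₂), in SDs of individual change:

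- 13 v 7: 2.101 × √(1/13 + 1/7) = 2.101 × 0.469 = 0.98
- 10 v 10: 2.101 × √0.2 = 0.94
- 16 v 4: 2.101 × √0.3125 = 1.17

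The contrast can reveal a large difference only. It serves estimation, not testing.

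**The case against.** The strongest reply is that the stated target is the personalised package as a whole. Giving NMN to some and not to others is part of that package, and the whole-group mean change is the right summary of it. This stands. A reader might infer that the model is mis-specified, but the article does not support that: the pooled mean is valid for the strategy and simply answers a different question.

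Several further points also stand:

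- NAD is not the only marker that might reflect a supplement. Untargeted plasma metabolomics is planned and could detect supplement-related compounds. Nor is it the only possible internal contrast, since urolithin A and the multivitamin are also assigned on baseline measures and could be compared on other outcomes.
- The contrast does not isolate NMN. NMN is assigned on VO2peak and not on NAD, so regression to the mean should have little influence on NAD change. But recipients are less fit, and everyone starts exercise, diet and sleep advice, whey, creatine and fucoidan together. Less fit people may respond differently to that package.
- Entry requires untrained people, which may put more than two thirds below the 50th percentile and shrink the dilution.
- At 13 v 7 and d = 1.0 the contrast has less power (57%) than the pooled test (70%).
- P values "values will be interpreted descriptively and hypothesis-generating only", individual trajectories are plotted, and no primary outcome depends on NAD.

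Finally, a full analysis plan that is not shown may contain a split by supplement. The point therefore rests on the model the article states for all continuous outcomes, and is not a claim that no such split exists anywhere. None of these points makes the pooled change informative about NMN, which is all that is claimed.

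**Conclusion.** The point holds as an inexpensive improvement to a stated analysis, of low to moderate weight. As stated, the NAD analysis yields the recipients' change diluted by the share not on NMN: 65% of it at 13 of 20, 80% at 16 of 20, undiluted at 20 of 20. These figures assume no NAD change in non-recipients and complete data. The actual share is not reported, so the actual dilution is unknown. The power figures also depend on the assumed d and a common SD.

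A reader might go further and infer that the planned model is wrong or that the trial's conclusions are biased. The article supports neither: the analyses are declared exploratory, and the pooled estimate is sound for what it estimates. Nor would the added contrast be a causal estimate of NMN's effect on NAD.

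**What to change.** Keep the pooled NAD estimate. For NAD only, fit one further model with NMN receipt at baseline and receipt-by-time, and report the change in recipients, the change in non-recipients and their difference, each with a 95% CI.

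- Make baseline to week 4 the main contrast, because it precedes any dose adjustment. Defining receipt at baseline also avoids a difficulty at week 8: Table 3's week-4 NMN rule does not say whether it applies only to those who started NMN.
- Tabulate baseline NAD by NMN assignment, which shows whether the VO2peak cut-off picks out people with lower NAD.
- Label the comparison exploratory and non-randomised, and state that recipients are less fit and that all participants start the other components together.
- Keep any week-8 listing by NMN dose descriptive, because escalation depends on the VO2peak response.
- Do not make the same split for VO2peak, on which recipients were selected.

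The cost is one extra model and a small table for an assay already planned, with no new visit, sample or change to treatment. The NAD measurement is described in the future tense, so this should be written down before the results are seen. The drawback is small groups and wide intervals.
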